#### Correlation analysis and regression modeling

2.9.4

Independent t-tests and chi-square tests will identify significant associations (p<0.05) between depression and demographic features, sleep patterns, or life events. Significant factors will be incorporated into binary logistic regression models to evaluate their relationship with adolescent depression.

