**Discussion:**

This prospective study evaluates AA’s efficacy in enhancing sleep quality and preventing depression in adolescents. The findings will elucidate AA’s potential clinical applications for adolescent insomnia treatment and depression prevention, thereby providing evidence to support its broader implementation in this population.

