#### Primary outcome

2.8.1

PSQI: The Chinese version of the PSQI will be used for assessment (25, 26), which has been proven to be highly reliable and effective in evaluating the sleep quality of Chinese adolescents (27).The PSQI covers seven key dimensions: sleep quality, sleep latency, sleep duration, sleep efficiency, sleep disturbances, use of sleep medication, and daytime dysfunction. The total score ranges from 0 to 21, with higher scores indicating poorer sleep quality. A PSQI score > 7 is used as the cutoff for sleep quality problems.

BDI: A 21-item scale designed to assess core depressive symptoms, evaluating clinical manifestations over the past two weeks to determine depression severity, with total scores ranging from 0 to 63. For non-clinical adolescent populations, a BDI score ≥20 indicates the presence of depressive symptoms (28, 29).

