### Statistical analysis

2.9

Statistical analyses will be performed using SPSS 25.0 (SPSS, Chicago, IL, USA). The incidence of adolescent depression will be calculated based on the Beck Depression Inventory (BDI) thresholds established in prior studies. Continuous variables will be presented as mean ± standard deviation, while categorical data will be expressed as percentages or proportions. A p-value <0.05 will be considered statistically significant for intergroup differences, and p<0.01 will indicate highly significant differences.

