#### Intergroup comparison methods

2.9.1

For normally distributed measurement data meeting the assumptions of parametric tests, within-group pre- and post-treatment comparisons will be conducted using paired-sample t-tests. Intergroup comparisons will employ one-way ANOVA. Non-normally distributed measurement data will be analyzed using nonparametric rank-sum tests, and categorical data will be assessed via chi-square tests or Fisher’s exact probability test. These comparisons will evaluate the therapeutic effects of auricular acupressure.

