#### Multi-timepoint data analysis

2.9.2

For repeated-measures data satisfying the sphericity assumption, repeated-measures ANOVA will be applied. If the sphericity assumption is violated, Greenhouse-Geisser correction or multivariate ANOVA will be used. This analysis will examine the main effect of time on outcome measures and potential time-by-group interactions.

For non-normally distributed data or datasets with significant missing values across timepoints, mixed-effects models will be employed. These models accommodate unbalanced data and missing values while accounting for intra-individual correlations.

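### Section 2.9.4 selects depression predictors by univariable p<0.05 and refits them on the same data, which biases the odds ratios of weak to moderate predictors and gives no adjusted treatment effect

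*Protocol article*

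**What the plan says.** Section 2.9.4 (Correlation analysis and regression modeling) fixes a selection rule and a model. The rule is: "Independent t-tests and chi-square tests will identify significant associations (p<0.05) between depression and demographic features, sleep patterns, or life events". The model follows: "Significant factors will be incorporated into binary logistic regression models to evaluate their relationship with adolescent depression". The candidates fall into three classes: demographics, sleep and life events. Treatment arm and baseline BDI are not named. The section does not say whether the data are those of the screened students or the randomised cohort, or which time point supplies the outcome.

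The effect of auricular acupressure (AA) on depression is handled elsewhere. BDI is a primary outcome, with the cut-off in section 2.8.1: "a BDI score ≥20 indicates the presence of depressive symptoms". Section 2.9 adds: "The incidence of adolescent depression will be calculated based on the Beck Depression Inventory (BDI) thresholds established in prior studies". Section 2.9.1, on comparisons between groups, says that "categorical data will be assessed via chi-square tests" or Fisher's test, and closes: "These comparisons will evaluate the therapeutic effects of auricular acupressure". Section 2.9.2 covers the repeated measures: "This analysis will examine the main effect of time on outcome measures and potential time-by-group interactions".

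**The concern.** When a variable enters a model only because it reached p<0.05 in the same data, its reported odds ratio is conditional on having looked large. Weak true predictors pass mainly when chance has pushed their estimate away from 1, so the published value is too extreme. The confidence interval takes no account of the selection. Null variables also pass, each with probability 5%, and are then reported beside the real ones.

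The second weakness is the missing arm term. If the outcome is depression after treatment, the model pools three differently treated groups without saying which group a participant was in. It then gives neither an adjusted treatment effect nor risk-factor estimates that allow for treatment.

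At stake is the quality of the risk-factor results that a randomised trial would publish on adolescent depression. The primary comparisons are not at stake. The rule is stated in full, so this is a weak stated method and not a detail left for a later document.

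**Working it through.** **The plan's own figures.** The protocol gives no number for this regression, so the sample comes from section 2.3, taking its 52 per group as given.
- Completers: 3 × 52 = 156.
- Randomised: 52 / (1 − 0.20) = 65 per group; 3 × 65 = 195.
- To be screened: 195 / 0.20 = 975.

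The last two steps reproduce the stated 65 and 975.

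**Assumption on the depression rate.** The documents give no rate of BDI ≥20 for this cohort. I take 20%, the Introduction's upper figure for mild to moderate depression among adolescents in general, with a range of 10% to 30%. At 20% the events are 156 × 0.20 ≈ 31 and 195 × 0.20 = 39.

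**Null factors passing the screen.** For k independent null candidates, P(at least one passes) = 1 − 0.95^k.
- k = 5: 1 − 0.95^5 = 0.23
- k = 10: 1 − 0.95^10 = 0.40
- k = 20: 1 − 0.95^20 = 0.64

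**Inflation of a true predictor.** Simulation, 800 runs per setting: ten independent standard-normal candidates, one of them truly predictive, a t-test screen at p<0.05, then a logistic fit on those that pass. Odds ratios are per SD and are averaged on the log scale.

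| N | Depression rate | True OR | Chance selected | Mean OR, no screen | Mean OR when selected |
|---|---|---|---|---|---|
| 156 | 20% | 1.25 | 22% | 1.26 | 1.71 |
| 156 | 20% | 1.5 | 48% | 1.50 | 1.79 |
| 156 | 20% | 2.0 | 90% | 2.02 | 2.11 |
| 195 | 20% | 1.25 | 25% | 1.25 | 1.60 |
| 195 | 20% | 1.5 | 62% | 1.53 | 1.70 |
| 195 | 20% | 2.0 | 96% | 2.03 | 2.07 |
| 156 | 10% | 1.5 | 31% | 1.51 | 2.08 |
| 156 | 30% | 1.5 | 61% | 1.51 | 1.71 |
| 975 | 20% | 1.25 | 79% | 1.26 | 1.29 |
| 975 | 20% | 1.5 | >99% | 1.50 | 1.51 |

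The column without the screen stays close to the truth, so the excess in the last column comes from the selection. A separate simulation with a single candidate (4,000 runs, N = 156, 20% depressed) agrees: a true OR of 1.4 is selected 39% of the time and then averages 1.75.

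A strong predictor is not fully protected if events are scarce. At N = 156 and a 10% rate, a true OR of 2.0 averages 2.43 when selected, against 2.10 without the screen.

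**The case against.** The strongest reply is that section 2.9.4 is a risk-factor analysis and should be judged as one. That stands. The abstract states the trial's aim as "This prospective study evaluates AA’s efficacy in enhancing sleep quality and preventing depression in adolescents", and a reader might infer that, because this is the only model stated with binary depression as its outcome and it has no arm term, the plan cannot test prevention. The documents do not support that. BDI-defined depression can be compared between arms by chi-square or Fisher's test under section 2.9.1, and BDI scores are covered by the time-by-group analysis in section 2.9.2. Neither uses the screened model. An unadjusted comparison is valid in a randomised trial, and section 2.9.3 allows covariate adjustment if dropouts and completers differ at baseline.

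Two other tempting readings also fail. One is that sleep variables measured after baseline would absorb the treatment effect: the section does not say that post-baseline values are used, and a model without an arm term has no treatment effect to absorb. The other is that arm would have to pass the p<0.05 screen and would often be dropped: the protocol does not say that arm is screened.

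The size of the bias is also open to challenge. All the scales are collected at baseline before insomnia is identified, so the model could be meant for the roughly 975 screened students, where inflation almost disappears for a true OR of 1.5 or more. No candidate count is given. Screening every subscale would give 27 candidates before demographics (PSQI 7, ASHS 9, ASWS 5, ASLEC 6), while screening totals would give few. Correlation between subscales would lower the false-entry figures. These points limit the size but do not rescue the method: a larger sample does not reduce the rate at which null factors pass.

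**Conclusion.** The concern holds as a criticism of the risk-factor model only. If that model is fitted in the randomised cohort, selected predictors with a true OR of 1.5 average 1.70 (N = 195) to 1.79 (N = 156) at an assumed 20% depression rate. At N = 156 the range is 1.71 to 2.08 over rates of 30% down to 10%. A true OR of 2.0 rises only to 2.07 to 2.11 at the 20% rate. The chance of at least one false entry is 23% to 64% for 5 to 20 independent null candidates.

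These figures rest on the assumed depression rate, independent normal candidates, one true predictor, and use of the randomised cohort. The model as written also gives no adjusted treatment effect. It is worth changing, but it does not touch the trial's between-arm comparisons.

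**What to change.** Remove the p<0.05 screen from section 2.9.4. Fit one logistic model with a short list of baseline covariates fixed in advance, for example baseline BDI, age or school level, sex, baseline ASLEC and baseline PSQI. State the sample and the time point. If the outcome is measured after randomisation, force arm into the model.

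That example has 7 parameters (two for arm, five covariates), or about 31 / 7 ≈ 4.5 events per parameter at 156 analysed and 20% depressed. The text should therefore specify penalised estimation, such as Firth's, if events are few. Label any wider search for risk factors exploratory. Say in one sentence that the effect of AA on depression is judged by the between-arm comparisons in sections 2.9.1 and 2.9.2.

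The cost is a change of analysis wording, with no added participants, visits or data. The downside is that fewer factors are examined in the main model.

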**Methods:**

This study is a single-center, double-blind, randomized controlled trial conducted in Nanjing, China. Participants are students from junior and senior high schools in Nanjing. A multi-stage stratified cluster sampling method is used to recruit students from 7th and 8th grades (junior high) and 10th and 11th grades (senior high). Baseline data will be collected using the Chinese version of the Pittsburgh Sleep Quality Index (PSQI), Beck Depression Inventory (BDI), Adolescent Sleep Hygiene Scale (ASHS), Children’s Depression Inventory (CDI), Adolescent Self-rating Life Events Checklist (ASLEC) and Adolescent Sleep-Wake Scale (ASWS), and insomnia patients will be identified. Adolescents who met the inclusion and exclusion criteria and whose guardians signed informed consent forms will be enrolled in the study. They will be randomly assigned to one of three groups: AA group, sham auricular acupressure (SAA) group, and control group. The treatment lasted for 8 weeks, with follow-up assessments at 3 and 6 months post-treatment. The primary outcome measures are PSQI and BDI scores, while secondary outcome measures included ASHS, CDI, ASLEC, and ASWS scores.

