Adolescence represents a critical developmental period characterized by significant alterations in sleep behavior. During this phase, adolescents experience physiological changes including delayed circadian rhythms and diminished homeostatic sleep regulation (7), culminating in a “perfect storm” of sleep disturbances manifested as delayed sleep onset, insufficient sleep duration, and difficulties in sleep maintenance (8). At the physiological level, the delayed maturation of the suprachiasmatic nucleus results in circadian phase delay, coupled with impaired homeostatic regulation of sleep need, leading to prolonged wakefulness in adolescents (8). Concurrently, psychosocial factors such as academic stress, social demands, and blue light exposure from electronic devices further disrupt sleep-wake cycles (9). Epidemiological studies have confirmed that sleep problems in adolescents significantly increase depression risk (10, 11), with this association being validated by a prospective cohort study in Guangzhou, China, demonstrating a dose-response relationship between reduced sleep duration (AOR=0.86, 95%CI: 0.80–0.92) and poorer sleep quality with subsequent depressive symptoms (12). Notably, while a bidirectional relationship exists between insomnia and depression (13), longitudinal studies more frequently indicate that insomnia precedes depressive onset, with some cases traceable to the perinatal period (14). Neurobiological research further reveals that decreased N3 sleep and diminished delta power during adolescent brain reorganization (15) may impair functional connectivity in emotion-regulation neural circuits (e.g., prefrontal-amygdala pathways), thereby establishing the neurobiological basis for insomnia-depression progression. Collectively, this evidence underscores the crucial need to develop adolescent-specific insomnia interventions for depression prevention.

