ASLEC: A self-rating scale for negative life events specifically developed for adolescents by Chinese experts. The ASLEC assesses life events in the past six months at baseline, covering 27 items across six domains of negative life events in adolescents: interpersonal relationships, academic pressure, family conflicts, and health. The scale has sufficient test-retest reliability and concurrent validity, with total scores ranging from 0 to 108 (33).

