#### Missing data handling and dropout analysis

2.9.3

Missing Data: Multiple imputation will be used to address missing data, leveraging intervariable correlations to generate plausible values and enhance result accuracy.

Dropout Analysis: The primary analysis will follow the per-protocol approach, including only subjects who adhered strictly to the study protocol. As a supplementary strategy, intention-to-treat (ITT) analysis will include all randomized participants regardless of protocol deviations or dropout status, preserving randomization integrity and minimizing selection bias. Additionally, baseline characteristics (e.g., age, sex, initial depression scores) of dropouts versus completers will be compared using chi-square or t-tests to assess systematic bias. Significant differences will prompt covariate adjustment in regression models.

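### The section 2.9.4 model for depression omits baseline BDI and names no visit, so it cannot tell a factor that adds to later depression risk from one that only marks existing low mood

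*Protocol article*

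**What the plan says.** All references are to the protocol article.

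- **Candidates and screen (2.9.4).** "Independent t-tests and chi-square tests will identify significant associations (p<0.05) between depression and demographic features, sleep patterns, or life events".
- **Model entry (2.9.4).** "Significant factors will be incorporated into binary logistic regression models to evaluate their relationship with adolescent depression". No covariate is entered regardless of the screen, and no visit is given for depression or for the factors.
- **Outcome (2.9 and 2.8.1).** "The incidence of adolescent depression will be calculated based on the Beck Depression Inventory (BDI) thresholds established in prior studies". The cut-off is in the primary outcome section: "For non-clinical adolescent populations, a BDI score ≥20 indicates the presence of depressive symptoms".
- **Baseline mood is available (Abstract, Methods).** "Baseline data will be collected using the Chinese version of the Pittsburgh Sleep Quality Index (PSQI), Beck Depression Inventory (BDI", followed by the other scales.
- **Baseline mood will vary.** The criteria in 2.2.1 and 2.2.2 exclude nobody on BDI score.
- **The only place where initial depression can enter a regression (2.9.3).** The plan compares "baseline characteristics (e.g., age, sex, initial depression scores" and similar variables between dropouts and completers, and adjusts if they differ significantly.
- **Direction of effect (Introduction).** "a bidirectional relationship exists between insomnia and depression", although the same sentence adds that longitudinal studies more often find insomnia coming first.
- **Life events (2.8.2).** "The ASLEC assesses life events in the past six months at baseline".

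**The concern.** Follow-up BDI usually depends strongly on baseline BDI. Adolescents with low mood at entry are also likely to report poorer sleep and more negative life events. A model for later depression that holds sleep and life events but not baseline mood will show associations for those factors even where they carry no information beyond mood at entry.

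The missing visit makes this worse. If the outcome is depression at follow-up, baseline BDI is the obvious omitted covariate. If outcome and predictors come from the same visit, the model cannot distinguish sleep as a precursor from sleep as a symptom.

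At stake is how the risk-factor analysis is read. The Introduction argues that insomnia predicts depression, and the Discussion aims to observe depression following insomnia. A table of significant sleep and life-event factors would probably be read as support for that rationale, whether or not those factors add anything to baseline mood.

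**Working it through.** **1. Does the plan bring in baseline BDI by another route?** The rule in 2.9.3 is the only candidate. It depends on a significant dropout-versus-completer difference, so it addresses attrition. If dropout is balanced on initial depression, nothing is adjusted. If it is unbalanced, adjustment follows for a reason unrelated to this question. The gap stays open.

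**2. How often would a factor with nothing to add be selected?** The plan states no figure to reproduce, so this is an illustration.

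From the protocol (2.3): 52 per group evaluable, 3 × 52 = 156; 65 per group randomised, 3 × 65 = 195.

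Assumed, because the documents give none of them:
- 20% above the BDI threshold at follow-up;
- r1, the correlation of the factor with baseline mood, 0.3 to 0.6;
- r2, the correlation of baseline with follow-up mood, 0.5 to 0.7;
- no association of the factor with follow-up mood once baseline mood is known.

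The factor's correlation with follow-up mood is then r1 × r2. Dichotomising follow-up mood at the 80th percentile multiplies it by φ(0.842)/√(0.2 × 0.8) = 0.280/0.4 = 0.70. The expected test statistic is about t = r√(n−2)/√(1−r²) with r = 0.70 × r1 × r2, and the chance of p<0.05 is about Φ(t − 1.96).

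- r1 = 0.3, r2 = 0.5, n = 156: r = 0.70 × 0.15 = 0.105; t = 1.31; chance 26%.
- r1 = 0.5, r2 = 0.6, n = 156: r = 0.70 × 0.30 = 0.21; t = 2.67; chance 76%.
- r1 = 0.5, r2 = 0.6, n = 195: t = 2.98; chance 85%.
- r1 = 0.6, r2 = 0.7, n = 195: r = 0.70 × 0.42 = 0.294; t = 4.27; chance 99%.

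A simulation with 600 runs per row, in which baseline mood generates the factor and no direct effect exists, agrees. Odds ratios are medians per SD of a factor scored so that higher means worse.

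| n | r1 | r2 | Passes t-test screen | OR without baseline mood | OR with baseline mood | Significant with baseline mood |
|---|---|---|---|---|---|---|
| 156 | 0.3 | 0.5 | 26% | 1.29 | 1.01 | 4.8% |
| 156 | 0.3 | 0.7 | 45% | 1.46 | 0.99 | 4.2% |
| 156 | 0.5 | 0.5 | 61% | 1.59 | 1.00 | 4.5% |
| 156 | 0.5 | 0.7 | 88% | 1.99 | 1.01 | 3.5% |
| 195 | 0.3 | 0.5 | 30% | 1.30 | 0.99 | 5.5% |
| 195 | 0.3 | 0.7 | 57% | 1.48 | 1.00 | 3.7% |
| 195 | 0.5 | 0.5 | 67% | 1.58 | 1.00 | 3.8% |
| 195 | 0.5 | 0.7 | 95% | 1.96 | 1.00 | 5.3% |

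Extending r1 to 0.6 takes the upper end to about 98% and the odds ratio to about 2.3.

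**3. Would removing pupils already above the threshold be enough?** Under the same assumptions, restricting to those below the cut at baseline still leaves selection in roughly 9% to 41% of trials and odds ratios of about 1.2 to 1.7. Mood still varies below the threshold.

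**4. What the illustration cannot show.** The same three correlations arise if baseline mood drives the factor (confounding) or if the factor drives baseline mood, which then drives later mood (mediation). In both cases the factor's correlation with follow-up mood is r1 × r2, so the figures are the same and the data cannot tell the two apart. The simulation shows what the omission does to selection, not which causal story is true.

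**The case against.** **Mediation.** Baseline ASLEC looks back six months and entry requires more than three months of insomnia, while BDI covers two weeks. Sleep problems and life events may therefore precede baseline mood and act through it. Adjusting for baseline BDI would then remove part of a real effect. This stands. It is a reason to report both models, not to omit the adjusted one.

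**Causal reading.** A reader might infer that the plan treats sleep and life events as leading to depression, or that the omission is confounding plain and simple. The documents do not support either. Section 2.9.4 is headed as correlation analysis and speaks only of association and relationship, and confounding cannot be told from mediation here. The claim is limited to what the model can separate.

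**Visit.** If 2.9.4 meant depression at baseline, baseline BDI would be the outcome and could not be a covariate. The word incidence in 2.9 points to follow-up but does not settle it. That is why the visit must be named.

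**Condensed article.** The full covariate list of a secondary model may sit in an analysis plan. But 2.9.4 states its factor groups and its entry rule, and baseline mood falls in none of the groups.

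**Size.** The range is wide and rests on assumed correlations. All participants have PSQI above 7, which would tend to weaken sleep-mood correlations, so the upper values are doubtful for PSQI. Nor would every distorted odds ratio exceed 1: on ASHS and ASWS higher scores are better, so theirs would fall below 1.

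**Conclusion.** The point holds in a limited form. As written, the 2.9.4 model leaves out a baseline value that the trial collects and that the protocol's own account links to both predictors and outcome, and it sets no order in time. It cannot show whether a sleep or life-event factor adds to the risk of later depression or only marks low mood already present.

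Under the assumed correlations and a 20% depression rate, a factor with no association beyond baseline mood would be selected in roughly 25% to 98% of trials, against about 5% with baseline mood in the model. The range shows that the problem can be large; it does not estimate its size in this trial.

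A reader might also infer that the treatment effect is compromised. It is not: the group comparisons of PSQI and BDI in 2.9.1 and 2.9.2 do not use this model. The consequence is confined to the secondary risk-factor conclusions. The change is worth making before analysis, but it does not threaten the trial's main result.

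**What to change.** In section 2.9.4:

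1. Define the outcome as depression by the BDI threshold at a named follow-up visit.
2. Take the sleep and life-event predictors from baseline.
3. Include baseline BDI, as a continuous score, in the main model whatever its p-value.
4. Report the model without baseline BDI beside it, and say that the two answer different questions: association beyond baseline mood, and total association including any path through baseline mood.
5. Describe any model with outcome and predictors from the same visit as association only.

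The cost is a few sentences; the data are already collected and nothing changes for participants. The downside is that adjusted associations will be smaller, and part of a true indirect effect may be removed. Reporting both models makes that visible.
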